#### Sample size

The sample size was calculated using two-way analysis of variance (ANOVA) for repeated measures by analyzing walking distance and the standard deviation in meters on the 6MWT from previously published data [15]. A two-tailed alpha error of 0.01 was implemented with a power of 95%, considering clinical improvement for COPD patients after PR and a difference of 30 m between groups on the walking test. For the calculations, the following means and standard deviations of the time observed in the 6MWT in the rehabilitation and control groups were used: pre-PR 312.43 ± 51.26 and post-PR 342.85 ± 48.82 m (rehabilitation group); pre-PR 305.13 ± 54.60 and post-PR 298.20 ± 52.81 m (control group), and a sample size of 32 subjects was found (effect size = 1.04). As the study of Elci et al. [15] was composed of two groups (rehabilitation and controls) and ours will be composed of three groups, we will assume that the 32 subjects will be part of the rehabilitation program (the PRIMTLL and PRIMTIVH groups), and 16 more subjects will be added as a study control group for a total sample of 48 subjects. In addition, 12 more subjects will be added into the study, because we will also assume a 20% loss to follow-up as well as 5% missing data, for a total sample size of 60 subjects.

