#### Statistics analysis

The Kolmogorov-Smirnov test will be performed to analyze sample normality, and two-way ANOVA followed by a Bonferroni post hoc test will be used to compare the differences among the groups. Data will be analyzed using the GraphPad Prism software version 5.0 (GraphPad Software Inc., San Diego, CA, USA). The significance level was set at 95% (*p* ≤ 0.05).

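### Splitting the 32 subjects from a two-group calculation into two arms of 16 leaves about 58% power at effect size 1.04 and two-sided alpha 0.01, not the stated 95%

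*Protocol article*

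**What the plan says.** The Sample size section gives the method as follows: "The sample size was calculated using two-way analysis of variance (ANOVA) for repeated measures", based on six-minute walk distance from a published two-group study. The error rates are given as "A two-tailed alpha error of 0.01 was implemented with a power of 95" per cent, with "a difference of 30 m between groups on the walking test" as the target. The source data are "pre-PR 312.43 ± 51.26 and post-PR 342.85 ± 48.82 m (rehabilitation group") and "pre-PR 305.13 ± 54.60 and post-PR 298.20 ± 52.81 m (control group"). The result is "a sample size of 32 subjects was found (effect size = 1.04").

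The section notes that the source study had two groups and this trial has three. Its adaptation is: "we will assume that the 32 subjects will be part of the rehabilitation program (the PRIMTLL and PRIMTIVH groups"). It adds 16 controls for a total of 48, then raises this to 60 for 20% loss to follow-up and 5% missing data. The power is not recalculated for three arms.

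The Statistics analysis section specifies two-way ANOVA with a Bonferroni post hoc test and a different error rate: "The significance level was set at 95" per cent, explained there as p ≤ 0.05.

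**The concern.** A sample size from a treated-versus-control calculation covers both sides of that comparison if it is a total, or one side if it is a per-group number. The plan follows neither reading. All 32 go to the two active arms, and a control arm half that size is added. Each of the three pairwise comparisons then has 16 against 16, whatever the 32 originally meant.

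The Abstract and Background say the trial should show which type of inspiratory muscle training (IMT) is most effective. That question rests on these pairwise comparisons. If their power is well below 95%, a null result would be read as strong evidence that adding IMT, or choosing one modality over the other, makes no difference. The data could not support that reading.

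**Working it through.** **Inputs (Sample size section):** effect size 1.04, metric not named; two-sided alpha 0.01; power 95%; 32 subjects; 16 per arm, from 48/3. From the Statistics analysis section: alpha 0.05 with Bonferroni. Taking three pairwise contrasts, which is an assumption about the family, gives 0.05/3 = 0.0167.

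**1. Reproducing 32.** Read 1.04 as a standardised mean difference d. The normal formula per group is

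n = 2(z₀.₉₉₅ + z₀.₉₅)²/d² = 2(2.576 + 1.645)²/1.04² = 32.9, so 33.

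The exact noncentral t gives 35 per group, or 70 for two groups. Power at 32 per group is 94.3% (normal) or 92.9% (t). So 32 is close to a per-group number and far from a two-group total.

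**2. Power with the planned arms.** Noncentral t, two-sided, d = 1.04, noncentrality d·√(n₁n₂/(n₁+n₂)):

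| Comparison | alpha 0.01 | alpha 0.05/3 | alpha 0.05 |
|---|---|---|---|
| 16 vs 16 (planned evaluable) | 58.0% | 65.8% | 81.2% |
| 15 vs 15 (25% of 60 lost) | 54% | 62% | 79% |
| 20 vs 20 (no losses) | 71.5% | 77.9% | 89.3% |
| 32 vs 16 (IMT arms pooled) | 75.7% | 81.5% | 91.4% |

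The normal approximation for 16 vs 16 at 0.01 is 64.3%. No entry reaches 95%.

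**3. Detectable effect at 16 per arm.** For 95% power, d must be about 1.58 at alpha 0.01 or 1.50 at 0.05/3. For 80% power at 0.05/3 it is about 1.20.

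**4. Could 1.04 be Cohen's f?** For two groups d = 2f = 2.08. A simple two-group test then needs 21 to 22 in total. Repeated-measures versions with two groups (between-group or interaction, correlation 0 to 0.8) need 6 to 19. None gives 32.

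**5. Does pre-post correlation rescue the total of 32?** From the quoted means, the difference in change is (342.85 − 312.43) − (298.20 − 305.13) = 30.42 + 6.93 = 37.35 m. The pooled SD over the four quoted SDs is 51.9 m. With correlation ρ, the SD of change is 51.9·√(2(1−ρ)). Results at 16 per arm and alpha 0.01:

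| ρ (assumed) | d for 37.35 m | Power | d for 30 m | Power |
|---|---|---|---|---|
| 0.50 | 0.72 | 26% | 0.58 | 15% |
| 0.76 | 1.04 | 58% | 0.83 | 37% |
| 0.80 | 1.14 | 68% | 0.91 | 45% |
| 0.85 | 1.31 | 82% | 1.06 | 60% |
| 0.90 | 1.61 | 96% | 1.29 | 81% |

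The quoted data give d = 1.04 at ρ of about 0.76, where power is 58%. They give 95% at 16 per arm only near ρ = 0.90, where d is about 1.6. Post-treatment values alone give 44.65/50.85 = 0.88, with 41% power.

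**The case against.** The strongest objection is that the calculation was a repeated-measures ANOVA, while the 58% comes from a two-sample t-test with 1.04 read as d. The protocol does not name the metric. If 1.04 were Cohen's f, 16 per arm would exceed 95% power. The standardised-difference reading also misses 32 exactly (33 or 35). A two-group total of 32 can be produced: the standard interaction formula with f = 1.04/2 = 0.52 and ρ = 0.15 returns 32 at alpha 0.01 and 95% power. On this view the fault is incomplete reporting, and power is a range rather than one number.

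Part of this stands. The 58% is conditional on reading 1.04 as a standardised mean difference, and with an unstated correlation the quoted means alone would allow anything from 26% (ρ = 0.5) to 96% (ρ = 0.9). The alternatives still do not restore the paragraph:

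- f = 1.04 gives totals well below 32. To match the quoted 37.35 m it would need a change SD of about 18 m, i.e. ρ of about 0.94.
- f = 0.52 is not the stated effect size. In the two-by-two interaction it implies a difference in change of 4 × 0.52 × 51.9 ≈ 108 m, against the quoted 37.35 m.
- ρ near 0.90 gives an effect size of about 1.6, which contradicts 1.04. With the stated 30 m it gives only 81%.

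It is also said that planning at 0.01 and testing at 0.05 errs on the safe side. That is true in direction, but even unadjusted 0.05 gives 81%. The Bonferroni family size is not stated, so 0.05/3 is an assumption.

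**Conclusion.** The concern holds. The stated effect size, alpha, power and number of subjects do not agree with one another once 16 per arm is used, and the power was never recalculated for three arms. Read as a standardised mean difference, 1.04 is the only reading tried that comes near 32 (as a per-group count) and also fits the source data, at ρ of about 0.76. On that reading pairwise power is about 58% at 0.01 and about 66% at 0.05/3. At 66%, a true effect of 1.04 SD would be missed about one time in three, while the protocol implies one in twenty. Using the normal approximation, retaining all 60 subjects or pooling the IMT arms does not bring power to 95% at alpha 0.01. The stated power also belongs to a test at 0.01 that the analysis section does not use.

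**What to change.** Keep n = 60 and rewrite the Sample size paragraph:

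- Use one alpha throughout: the 0.05 of the analysis section, with Bonferroni over the three pairwise contrasts, and state that family.
- Delete the claim of 95% power at alpha 0.01.
- Name the effect-size metric and state any pre-post correlation assumed, with its source.
- Report the power held at 16 evaluable per arm: about 66% for a standardised difference of 1.04 at alpha 0.05/3. If the authors can document a different metric or correlation, they should recompute this figure and show it.
- Report the detectable effect at 16 per arm and alpha 0.05/3: about 1.20 SD for 80% power and 1.50 SD for 95%.

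The cost is one reworded paragraph and a less favourable power statement; no extra patients are needed and the arms do not change. For comparison, holding 95% power at 0.01 for d = 1.04 would take 33 to 35 per arm: 99 to 105 evaluable, or 124 to 132 enrolled after dividing by 0.80.

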All three groups will submit to a conventional rehabilitation program consisting of aerobic exercise on a treadmill. For the first week, the subjects will perform 20 min of activity. A resting period lasting 2 min maximum will be allowed whenever requested by the subject. The training time will be increased after the 5th week to reach 30 min of daily activity [15]. Aerobic exercise will be performed on a treadmill, with a velocity corresponding to 70% of the maximum velocity achieved in the Incremental Shuttle Walking Test (ISWT) [16]. Ten percent of the starting time (2–3 min) of the training will be at a speed of 40% of the maximum speed reached in the ISWT for heating, 80% of the training time (17–25 min) will be at the target speed (70% ISWT), and the remaining 10% of the time will be cooling, with the same speed as for heating, reducing the speed to zero at the end of the training period [17, 18]. The physical activity training will be interrupted whenever the degree of dyspnea sensation reaches 4–6 (intense) on the Borg scale [14] or the heart rate (HR) exceeds 85% of the individual maximum HR value (220 – age). If the saturation drops (SpO_2_ < 90%) [19] during the exercise, we will administer supplemental oxygen at minimal flow with a nasal cannula to maintain higher than 90% saturation. The patients will be monitored every 5 min. Participants will be instructed to maintain aerobic activities on days that they are not performing the supervised PR program. Strength training for lower and upper limb muscles will be performed through a program consisting of 3 sets of 12 repetitions, initially using 60% of 1 maximal repetition (1RM), and this load will be increased to 70% by the 5th week and 80% in the 8th week of training [20]. For the upper limbs the training will be directed to the biceps, triceps, pectoral, and deltoid muscles, and for the lower limbs, the training will be for quadriceps and triceps femoris [3]. Guidance in energy conservation techniques as well as educational speeches regarding self-management of the disease will be provided [13]. The PRWIMT group will perform PR and IMT without any load; the PRIMTLL group will perform PR and IMT with a linear load; the PRIMTIVH group will perform PR and IMT with isocapnic voluntary hyperpnea.

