##### PRWIMT protocol

The PRWIMT protocol consists of conventional PR as previously described. Individuals will also perform a placebo IMT using a POWERbreathe® device (POWERbreathe International Ltd., Southam, UK) without any load for 3 cycles of 12 repetitions.

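### The 95% power is for rehabilitation versus control, but all three arms receive rehabilitation, so it applies to no between-arm comparison in this trial

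*Protocol article*

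**What the plan says.** The Sample size section sets the error rates ("A two-tailed alpha error of 0.01 was implemented with a power of 95"%) and names "a difference of 30 m between groups on the walking test". For the inputs it says that "the following means and standard deviations of the time observed in the 6MWT in the rehabilitation and control groups were used":

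- rehabilitation: "pre-PR 312.43 ± 51.26 and post-PR 342.85 ± 48.82 m (rehabilitation group")
- control: "pre-PR 305.13 ± 54.60 and post-PR 298.20 ± 52.81 m (control group")

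This gives 32 subjects at an effect size of 1.04. Because the source study had two groups and this trial has three, the section continues: "we will assume that the 32 subjects will be part of the rehabilitation program (the PRIMTLL and PRIMTIVH groups"). It adds 16 subjects as the control group, giving 48, and then 12 for losses, giving 60.

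The Intervention section describes a different kind of control. "All three groups will submit to a conventional rehabilitation program consisting of aerobic exercise on a treadmill", and "The PRWIMT protocol consists of conventional PR as previously described", with a no-load placebo IMT on top. The Strengths and limitations section gives the aim as finding what IMT adds to conventional rehabilitation. The Statistics analysis section compares the groups by two-way ANOVA with Bonferroni post hoc tests at the 0.05 level.

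**The concern.** The sample size treats PRWIMT as the counterpart of the source study's control group. It is not one: it receives the same treadmill, strength and education program as the other two arms. What separates the source groups is rehabilitation. What separates the arms here is IMT added to rehabilitation, or one IMT mode against the other. A benefit shared by all arms drops out of every difference between them.

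At stake is the credibility of the power statement. The trial is meant to tell therapists which IMT mode, if any, to add to rehabilitation. A 95% power figure that belongs to another comparison gives no basis for interpreting a non-significant result. This point is independent of how the 32 was split between arms and of the 0.01 versus 0.05 alpha; it would remain if both were settled.

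**Working it through.** **1. The source contrast**

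- Rehabilitation: 342.85 − 312.43 = +30.42 m
- Control: 298.20 − 305.13 = −6.93 m
- Difference in change: 30.42 − (−6.93) = 37.35 m

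**2. Reproducing the plan's figure**

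For a two-group comparison with d = 1.04, two-sided alpha 0.01 and 95% power, the requirement is 35 per group by the noncentral t (33 by the normal approximation). The figure of 32 is therefore close as a per-group number, but the article uses it as the total of two arms. With 16 per arm and d = 1.04, power is 58% at 0.01 and 81% at 0.05. That is a separate matter and is not counted here.

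Nor does 1.04 follow from the quoted means and SDs alone. The pooled post-PR SD is √[(48.82² + 52.81²)/2] = 50.85 m, and 37.35/50.85 = 0.73, 44.65/50.85 = 0.88 (post-PR means, 342.85 − 298.20), 30/50.85 = 0.59. A value of 1.04 needs an SD of 37.35/1.04 = 35.9 m, or 30/1.04 = 28.8 m. The article states neither.

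**3. Which effects the arms share**

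| | Rehabilitation | Loaded IMT or hyperpnea |
|---|---|---|
| Source: rehabilitation | yes | not stated |
| Source: control | contrasted with rehabilitation; distance fell | not stated |
| PRWIMT | yes | no (no-load placebo) |
| PRIMTLL | yes | yes |
| PRIMTIVH | yes | yes |

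The 37.35 m is a difference down the Rehabilitation column of the source. In this trial that column is constant. As an illustration, suppose PRWIMT gains the source study's 30.42 m. An IMT arm would then have to gain 30.42 + 37.35 = 67.77 m to show the source contrast, or 30.42 + 30 = 60.42 m to show 30 m, about twice the source rehabilitation gain.

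**4. What 16 per arm delivers for 30 m**

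Pairwise two-sample t on change, df = 2 × 16 − 2 = 30, noncentrality (30/SD) × √(16/2). Assumed change SD: 35.9 m as the central value, 25 m as a favorable limit with no source in the article, and 51 m from the pooled post-PR SD.

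| Two-sided alpha | SD 25 m | SD 35.9 m | SD 51 m |
|---|---|---|---|
| 0.01 (sizing) | 74% | 37% | 16% |
| 0.05/3 = 0.0167 (Bonferroni, three pairs) | 80% | 44% | 21% |
| 0.05 unadjusted | 91% | 63% | 36% |

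No cell reaches 95%. With no losses at all (20 per arm) and SD 35.9 m, the three figures are 48%, 56% and 73%.

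**5. Detectable difference and precision at 16 per arm**

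Detectable difference = d × SD, where d is the standardized effect giving 80% power. CI half-width = t × SD × √(2/16).

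- Bonferroni: d = 1.20, t = 2.536. At SD 35.9 m: 1.202 × 35.9 = 43 m (30 to 61 m for SD 25 to 51 m); half-width 2.536 × 35.9 × 0.3536 = 32 m (22 to 46 m).
- Unadjusted 0.05: d = 1.02, t = 2.042. At SD 35.9 m: 37 m (26 to 52 m); half-width 26 m (18 to 37 m).

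**The case against.** The best defense is that the section names 30 m between groups. A target difference can be chosen because it matters clinically; it need not be an expected effect, and the source may have been used only for variability. That reading has some support, since the section opens by saying that the source supplied walking distance and its SD. But the same section ties the 30 m to improvement after rehabilitation and says that the rehabilitation and control means were used. Even taken as a free-standing target, 30 m does not have 95% power at 16 per arm anywhere in the SD range shown.

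It can also be said that the article never states outright that the source controls had no rehabilitation. True; but it contrasts them with the rehabilitation group, and their distance fell.

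Two objections stand and limit the point. A reader might infer that the trial would miss any realistic benefit of IMT. The article does not support this: it gives no add-on effect, so nobody can say from it what is realistic, and under the most favorable assumptions (SD 25 m, unadjusted 0.05) power for 30 m is 91%. A reader might also attribute the whole shortfall in step 4 to the borrowed effect. Those powers also reflect 16 per arm and the alpha chosen. The borrowed effect on its own has no calculable power loss, because the correct effect is unknown.

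**Conclusion.** The point holds in this form: the 95% power belongs to rehabilitation versus control, a contrast absent from this trial, and it cannot be claimed for any comparison among the three arms. That conclusion rests on the article's text alone and needs no assumption about SD or effect.

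The size does rest on assumptions. For the one difference the article names, 30 m, power is about 37% at alpha 0.01, 44% under Bonferroni and 63% at unadjusted 0.05. These assume 16 evaluable per arm, a pairwise t-test on change and a change SD of 35.9 m, which is only implied by 37.35/1.04. Over SD 51 to 25 m the ranges are 16 to 74%, 21 to 80% and 36 to 91%. The conduct of the trial and its estimates are unaffected; the error is in the planning justification.

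**What to change.** In the Sample size section:

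1. Delete the claim of 95% power for the between-group difference.
2. State that the source effect is rehabilitation versus control, and stop equating PRWIMT with that control.
3. State instead what 16 evaluable per arm gives for IMT added to rehabilitation under the planned Bonferroni pairwise tests: about 43 m detectable with 80% power (30 to 61 m for SD 25 to 51 m) and an adjusted CI half-width of about 32 m (22 to 46 m). If unadjusted 0.05 figures are shown as well, label them as such: about 37 m (26 to 52 m) and 26 m (18 to 37 m).
4. Label the change SD as an assumption.
5. Commit to reporting each add-on effect with its confidence interval, and not to reading a non-significant result as absence of an IMT effect.

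The cost is rewording and a less favorable power statement. No extra patients and no change in procedures are needed.

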**Methods:**

This study is a blinded-investigator randomized controlled clinical trial. Sixty subjects will be randomly allocated into three groups: (1) pulmonary rehabilitation (PR) associated with inspiratory muscle training without any load (PRWIMT), (2) PR associated with inspiratory muscle training with a linear load (PRIMTLL), and (3) PR associated with inspiratory muscle training with isocapnic voluntary hyperpnea (PRIMTIVH). The protocol will be performed 5 days a week (3 days with supervision) for 10 weeks. The study will assess anthropometric data, lung function, respiratory muscle strength, and functional capacity by the Incremental Shuttle Walking Test and the Six-Minute Walk Test, lung volumes during the submaximal endurance test, peripheral muscle strength of the upper and lower limbs, dyspnea, and quality of life related to health, before and after the training protocol. Normality will be tested using the Kolmogorov-Smirnov test, and variables will be compared by two-way analysis of variance. The significance level was set at *p* < 0.05. Ethics approval was obtained from the Institutional Ethics Committee in Research (1.663.411). The study results will be disseminated through presentation at specific scientific conferences and publication in peer-reviewed journals.

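### Sixty enrolled subjects do not cover both stated losses: with 20% loss to follow-up plus 5% missing data about 45 remain evaluable, not the 48 required

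*Protocol article*

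**What the plan says.** The Sample size section of the protocol article builds the total in three steps. A power calculation on six-minute walk distance gives 32 subjects, who are assigned to the two groups that receive active inspiratory muscle training. A control group of half that number is then added: "16 more subjects will be added as a study control group for a total sample of 48 subjects". Finally the total is raised for losses: "In addition, 12 more subjects will be added into the study", and the reason given is that "we will also assume a 20% loss to follow-up as well as 5% missing data, for a total sample size of 60 subjects".

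The abstract repeats the total: "Sixty subjects will be randomly allocated into three groups". Study design describes a randomisation list numbered 1 to 60. The Subjects section says that participants who stop the programme, are absent for more than a week or do not attend reevaluation are excluded, so those lost do not return as evaluable.

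**The concern.** The section names a target, two loss rates and a total, and the three do not agree. Losses fall on the people enrolled. A target is therefore protected by dividing it by the share expected to remain, and 60 is too few once both rates are applied. A reader would take 60 as securing 48 evaluable subjects, when under the protocol's own assumptions it does not. With only about 16 per arm planned, even one subject per arm is worth stating correctly, and any power claim should refer to the number expected at analysis.

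**Working it through.** Inputs, all from the Sample size section unless noted:

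- Required before losses: 32 + 16 = 48, or 16 per arm over three arms.
- Loss to follow-up: 20%. Missing data: 5%.
- Added for losses: 12. Total enrolled: 60.
- Three arms (abstract). Equal allocation is assumed here, because the article does not state the ratio.

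**Reproducing the stated 60.** Two routes lead to it:

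- Add the two rates and apply them to the target: 48 × (1 + 0.25) = 60. The addition is 0.25 × 48 = 12, which matches the text.
- Divide by the share retained after the 20% loss alone: 48/(1 − 0.20) = 60. This is a correct inflation for that one loss and makes no allowance for the 5%.

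The article does not say which was used. The first uses both stated rates and so looks the more likely.

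**What 60 enrolled deliver under the stated losses.**

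- Rates added: 60 × (1 − 0.25) = 45, and 45/3 = 15 per arm.
- Rates in sequence: 60 × 0.80 × 0.95 = 45.6, and 45.6/3 = 15.2 per arm.
- 20% loss only: 60 × 0.80 = 48, or 16 per arm.

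The shortfall is 48 − 45 = 3 (2.4 in sequence), and it disappears only when the missing-data allowance is dropped.

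**What would retain 48 under both losses.**

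- Rates added: 48/0.75 = 64.
- Rates in sequence: 48/0.76 = 63.2, rounded up to 64.
- With three equal arms of 16 evaluable: 16/0.75 = 21.3 and 16/0.76 = 21.05, both rounded up to 22 per arm, so 3 × 22 = 66.

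**Illustration of the effect on power.** An independent two-sample t-test at a standardised difference of 1.04 (the effect size printed in the section) and two-sided alpha 0.01 has power of about 0.580 with 16 per arm and 0.541 with 15 per arm, a fall of about 4 percentage points. This is not the protocol's own calculation. The section names a two-way repeated-measures ANOVA, does not give the within-subject correlation and does not say what the 1.04 is standardised by.

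**The case against.** Three points can be made for the plan.

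First, no formula is shown, and 60 is exactly 48/0.80. A reader might infer that the authors certainly multiplied by 1.25 where they should have divided. The document does not establish that. This point stands, and the source of the 60 has to be left open. It does not rescue the sentence, because dividing by 0.80 leaves no room for the missing data that the same sentence says the 12 subjects cover. Nor does it help to read the 25% as a share of the 48: losing 12 of 60 is a 20% loss among those enrolled, and the text does not put it that way.

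Second, missing data need not mean a lost participant. The trial records many measures, and a gap in one of them may leave walking distance intact. Some missing post-tests may already sit within the 20%, since those who miss reevaluation are excluded. The article does not say what the 5% is a share of. This point stands in part. Forty-five is the lower end of a range of 45 to 48, reached if every subject with missing data drops out of the primary analysis. It is nevertheless the natural reading, because the 5% appears in the sample-size paragraph as an addition to the 20% and as a reason for enrolling more people.

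Third, a reader might infer a specific loss of trial power, or take this as proof that the trial is underpowered. The documents do not support either. The t-test figures are not the planned analysis, and whether 32 was derived and divided across the arms correctly is a separate question that adds no weight here.

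**Conclusion.** The point holds as an inconsistency within the Sample size section: 60 enrolled, with both stated losses applied, do not yield the stated 48. The size is modest, about 3 evaluable subjects in total (2.4 if the losses apply in sequence), or roughly one per arm. Put the other way, enrolment is 4 below what the target needs, or 6 below with three equal arms. The conclusion takes the 48 as given and assumes that both losses remove subjects from the primary analysis; the per-arm figures also assume equal allocation. It does not depend on which formula produced the 60, nor on any power model.

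**What to change.** Keep 60 and correct the sentence in one of two ways:

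- State that 60 enrolled are expected to yield about 45 evaluable subjects (about 15 per arm) under 20% loss to follow-up plus 5% missing data, and restate power at that number from the sponsor's own repeated-measures calculation, giving the within-subject correlation used.
- Or state that 60 covers a combined loss of 20%, missing data included, and so retains 48.

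Either version should say whether the 5% refers to subjects without a usable primary outcome. The cost is one sentence and, for the first option, one rerun of an existing calculation and a slightly less favourable stated figure. Design, enrolment and analysis do not change. Enrolling 64 (66 with equal arms) would also remove the discrepancy, but it means more recruitment and is not needed to make the text correct.
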